#### **2.5.4 Risks to study personnel**

The main risks to study personnel are from accidental exposure to blood and body-fluid borne infections. SOPs for staff safety are used in clinical and laboratory areas, including sharps management, hazardous waste management, etc. Universal precautions are used for handling all body fluids.

## **3 OBJECTIVES**

### **3.1 Study Objectives**

#### **3.1.1 Overall study objective**

Identification of an optimal pediatric dose of FMP2.1/AS02A that is safe, with high immunogenicity and acceptable reactogenicity.

#### **3.1.2 Primary specific objective**

Evaluate the safety and reactogenicity of FMP2.1/AS02A in children naturally exposed to *P. falciparum* malaria infection.

#### **3.1.3 Secondary specific objectives**

Measure the magnitude and duration of antibody response to FMP2.1 by ELISA assay.

### **3.2 Study Outcome Measures**

#### **3.2.1 Primary Outcome Measures**

1. Occurrence of solicited symptoms after each vaccination during a 7-day surveillance period (day of vaccination and days 1, 2, 3 and 7 after vaccination)
2. Occurrence of unsolicited symptoms after each vaccination during a 30-day surveillance period (day of vaccination and 30 subsequent days)
3. Occurrence of serious adverse events throughout the study period

#### **3.2.2 Secondary Outcome Measures**

1. Titers and activity of anti-FMP2.1 antibody at each time point where serology samples are analyzed, measured by ELISA.

## 4 STUDY DESIGN

### 4.1 Overview

- Randomized, controlled, dose-escalation phase I study
- One study center
- 100 healthy children aged 1-6 years residing in the rural town of Bandiagara, Mali
- Safety oversight from a DSMB and LMM
- Study monitoring by DMID
- Screening will be done within 35 days prior to the first immunization
- Dose escalating by 10 µg, 25 µg and 50 µg of FMP2.1 adjuvanted with 0.1 mL, 0.25 mL and 0.5 mL of AS02A, respectively
  - 20 children will be randomized to receive either the 10 µg dose of FMP2.1/AS02A (n=15) or rabies vaccine (n=5)
  - 40 children will be randomized to receive either the 25 µg dose of FMP2.1/AS02A (n=30) or rabies vaccine (n=10)
  - 40 children will be randomized to receive either the 50 µg dose of FMP2.1/AS02A (n=30) or rabies vaccine (n=10)
- Immunization schedule will be on study days 0, 30 +/- 7, and 60 +/- 7
- Each consecutive immunization with the 25 µg or 50 µg dose level of FMP2.1 will be administered at least 14 days after the corresponding immunization with the 10 or 25 µg dose of FMP2.1, respectively, to permit review of day 7 safety laboratory results.
- Route of immunization will be left deltoid muscle IM
- Source documents will be derived from the electronic CRFs. This will contain all the protocol required information including clinical laboratory test results and adverse event medical records. The information in the source document will then be entered directly into the Internet data system.
- Study duration will be approximately 14 months per participant

- 7-day surveillance after each immunization (day of vaccination and study days 1, 2, 3 and 7 for solicited adverse events)
- 30-day surveillance after each immunization for unsolicited adverse events
- Follow-up of serious adverse events (SAEs) until resolution or stability
- Beginning Study Day 120, participants will be visited and assessed by local guides at home at monthly intervals and return to clinic every three months for safety surveillance.
- The primary unblinded analysis will be conducted for all primary and secondary endpoints at a data-lock-point one month post Immunization 3 (study day 90), after which the Primary Study Report will be produced.
- The study will then continue in a single-blind fashion. Data gathered during this period will be reported in an addendum report.
- At the end of the study participants and their parents/guardians will be informed which vaccine they received and those who received malaria vaccine will be offered immunization with the rabies vaccine.

## **5 STUDY ENROLLMENT AND WITHDRAWAL**

### **5.1 Site description**

Participants for this study will be drawn from the population of healthy children aged 1-6 years residing in the town of Bandiagara, which has been the site of MRTC malaria studies since 1993. Bandiagara (pop. 13,364), is a rural town 700 km northeast of Bamako, the capital of Mali. In a census conducted in 1999, the predominant ethnic group is Dogon (64%) followed by Peuhl (12%), Bambara (6%) and 16 other ethnic groups. About 85% of residents reported their religion to be Islam, and about 8% reported belonging to various Christian denominations. Animist beliefs and practices are also common. The most common occupations among men were in agriculture (30%) with 21% in the commercial sector, mostly self-employed as vendors of various goods, and the rest reported a wide variety of occupations including 6% who were government workers and smaller numbers of teachers, health workers, traditional healers and practitioners of spiritual and magical arts. Nearly 80% of women reported their occupation as housewife, but it is evident to the casual observer that a large proportion of the women in Bandiagara are also working in agriculture and/or as producers and sellers of various goods. Forty-six percent of adults had received no formal schooling, and only 14% reported themselves to be literate. However, 86% of children of the age to be in primary school (7-11 years) were attending school. Seventy-five percent of marriages were reported to be monogamous and 25% were polygamous with 2-4 wives.

The annual per capita income for Mali as a whole is estimated to be \$600. However, this figure is based on large segments of the population who live in remote rural areas with virtually no cash economy, and per capita income in Bandiagara is higher than this. Income data specifically for Bandiagara are not available, but Bandiagara is a relatively affluent town by Malian standards, with a lively market economy and a significant tourist trade. Most homes are single story structures made of mud brick and/or concrete organized into compounds with several small dwellings surrounding a central courtyard. A main road runs through the length of the town, which extends about 2 km from end to end. All homes of potential participants in this trial are within walking distance of the BMP research clinic.

Since 1998 Bandiagara has been the site of an NIAID-supported contract for developing a site for testing malaria vaccines, known as the Bandiagara Malaria Project (BMP). Support for the BMP through the year 2010 is provided by a cooperative agreement from NIAID awarded to the Universities of Maryland and Bamako, with supplemental support from USAID, to conduct Phase 1 and 2 pediatric trials of the FMP2.1/AS02A malaria vaccine. The BMP has completed censuses of Bandiagara, established a laboratory with the capability of preserving sera, peripheral blood mononuclear cells (PBMCs), live parasites and DNA; and a clinical research center where malaria diagnosis and hemoglobin and blood glucose levels are routinely determined and where children with severe malaria are hospitalized and cared for. Thousands of children have been included in malaria research studies and treated for uncomplicated and severe malaria (5;6;51-53). Loss to follow-up has consistently been less than 7%.

The BMP research clinic is on the campus of the Bandiagara District Hospital, where two buildings were renovated in 2003 for the first of two NIAID-supported malaria vaccine clinical trials that have been conducted. The clinical research facility includes an air-conditioned clinical laboratory and vaccine storage preparation room, six private consultation rooms, a procedure room, covered waiting area, two vaccination rooms, a resuscitation suite, an observation room, and storage and administrative space. Locked cabinets with restricted access are used for data storage.

The BMP team has been managing severe malaria at this site since 1998, providing 24-hour inpatient care. In addition to the present capacity for 24-hour nursing care and physician coverage, and laboratory tests for hematological and biochemistry parameters, new and upgraded pediatric inpatient care facilities are being established for this trial including capacity for blood transfusion and oxygen supplementation. Children requiring X-rays will be transported to the District Hospital in Mopti, 60 km from the site on a paved road. Children requiring diagnostic or therapeutic interventions not available locally will be transported to the National Pediatric Hospital Gabriel Toure in Bamako.

The BMP team has been trained to conduct GCP-compliant studies, using source documents, written informed consent and standardized case report forms. The site has been monitored several times by DMID's contractor PPD, Inc., the US Army, and GSKBio as well as by the World Health Organization. The BMP team has also established a strong trust and rapport with the community, which is very accepting of conducting malaria vaccine trials there.

The site is connected to the MRTC central laboratory in Bamako via a VSAT system, which allows high-speed communication link with Bamako, US partner institutions and the Internet. Back-up Internet service for E-mail is available locally.

## **5.2 Subject Inclusion Criteria**

- Age 1-6 years inclusive at the time of screening
- Residing in Bandiagara town
- Appear to be in generally good health based on clinical and laboratory investigation
- Separate written informed consent obtained from the parent/guardian before screening and study start, respectively
- Available to participate in follow-up for the duration of study (14 months)

## **5.3 Subject Exclusion Criteria**

- Previous vaccination with an investigational vaccine or a rabies vaccine

- Use of a investigational or non-registered drug or vaccine other than the study vaccine(s) within 30 days preceding the first study immunization, or planned use up to 30 days after the third immunization
- Chronic administration (defined as more than 14 days) of immunosuppressants or other immune-modifying drugs within six months prior to the first immunization. This includes any dose level of oral steroids or inhaled steroids, but not topical steroids
- Confirmed or suspected immunosuppressive or immunodeficient condition, including human immunodeficiency virus (HIV) infection
- Confirmed or suspected autoimmune disease
- History of allergic reactions or anaphylaxis to immunizations or to any vaccine component
- History of serious allergic reactions to any substance, requiring hospitalization or emergent medical care
- History of allergy to tetracycline, doxycycline, nickel or Imidazole
- History of splenectomy
- Laboratory evidence of liver disease (alanine aminotransferase [ALT] greater than the upper limit of normal of the testing laboratory = 49.6 U/L).
- Laboratory evidence of renal disease (serum creatinine greater than the upper limit of normal of the testing laboratory = 0.5 mg/dL (44.2  $\mu$ mol/L), or more than trace protein or blood on urine dipstick testing).
- Laboratory evidence of hematologic disease (absolute leukocyte count  $<5,300/\text{mm}^3$  or  $>15,300/\text{mm}^3$ , absolute lymphocyte count  $<2,300/\text{mm}^3$ , platelet count  $<133,000/\text{mm}^3$ , or hemoglobin  $<9.0$  g/dL).
- Chronic skin condition that could interfere with vaccine site reactogenicity assessment
- Administration of immunoglobulins and/or any blood products within the three months preceding the first study immunization or planned administration during the study period.
- Simultaneous participation in any other interventional clinical trial
- Acute or chronic pulmonary, cardiovascular, hepatic, renal or neurological condition, severe malnutrition, or any other clinical findings that in the opinion of the PI may increase the risk of participating in the study
- Other condition that in the opinion of the PI would jeopardize the safety or rights of a participant in the trial or would render the participant unable to comply with the protocol

### **5.3.1 Rationale for using clinical assessment of immunosuppression**

We will not test for HIV routinely at the time of screening. HIV seroprevalence is 1.7% in Mali, one of the lowest rates in sub-Saharan Africa. Although no serosurveys have been done in Bandiagara, this site is in a remote rural area and almost certainly has a lower prevalence rate than the average for Mali. After working at this site for the past nine years, we have only very rarely encountered young adults, and virtually no young children, with illnesses that raised clinical suspicion of an immunosuppressive disease. In addition, the age distribution of HIV infection in Africa is bimodal, with most infection detected in young infants infected through maternal-to-child transmission or in sexually active teens and adults. Infection in children aged 1-6 years is almost certainly extremely rare in this setting. Therefore, testing for HIV would likely yield few, if any, cases of HIV in this small study.

This study is intended to produce comparable results to other Phase 1 trials of recombinant protein blood stage malaria vaccines adjuvanted with AS02A, including recent and ongoing trials conducted in Kenya and Mali. In these studies, a similar approach was taken to exclude persons with clinical evidence of immunosuppressive disease but not test for asymptomatic HIV infection, based on the rationale that it is necessary to assess the safety and immunogenicity of this vaccine in generally healthy persons who are representative of the population from which they are drawn. In Kenya, where rates of HIV infection are much higher, this general population includes many persons living with HIV and a study that excluded them would be of less value. Eventually, it will be necessary to demonstrate the safety and immunogenicity in persons living with HIV for any malaria vaccine to be employed in Africa, but because of the low rates of HIV infection in Mali these studies will have to be conducted elsewhere. Meaningful subanalyses of HIV-infected and uninfected vaccinees are not possible in this small trial.

Voluntary counselling and testing for HIV by rapid test is now available at the Bandiagara District Hospital, and antiretroviral treatment is available at the nearby Mopti District Hospital. In the event that HIV infection is suspected at the time of screening or later in the trial, participants and their parents/guardians will be referred to these sources of HIV testing and treatment.

## **5.4 Treatment Assignment Procedures**

### **5.4.1 Randomization Procedures**

Individual participants will be randomized to receive one of three escalating doses of FMP2.1/AS02A, or rabies vaccine. One hundred participants will be assigned to Cohort 1 (n=20), Cohort 2 (n=40) or Cohort 3 (n=40) in the order they are enrolled with stratification for age by two-year increments (1-2 years, 3-4 years, 5-6 years) but without stratification for gender, and randomized within cohorts to receive FMP2.1/AS02A or rabies vaccine. Because cohort sizes are not divisible by three, the numbers in each stratum may be either 6 or 7 in each age stratum for Cohort 1 and either 13 or 14 in Cohorts 2 and 3. Cohort 1 will be randomized in a 3:1 ratio to receive 10µg of FMP2.1 adjuvanted with 0.1 mL of AS02A (n=15) or rabies vaccine (n=5). Cohort 2 will be randomized in a 3:1 ratio to receive 25µg of FMP2.1 adjuvanted with 0.25 mL of AS02A

(n=30) or rabies vaccine (n=10). Cohort 3 will be randomized in a 3:1 ratio to receive 50µg of FMP2.1 adjuvanted with 0.50 mL of AS02A (n=30) or rabies vaccine (n=10). The total sample size for the rabies group will thus be 25.

Within each cohort, treatments will be assigned to participant ID numbers in randomized blocks of a size that will not be stated in this protocol to avoid compromising masking, per DMID guidelines. Randomization to either of the two vaccines will be done using a computer-generated randomization list. The randomization list will contain sequential codes linking a participant ID number to a vaccine assignment. Participant ID numbers will be assigned to participants of each cohort in the order in which they are enrolled in the trial.

#### **5.4.2 Masking Procedures**

Measures will be taken to keep participants, their parents/guardians and clinical investigators (including the PI) and all other staff involved in measuring study outcomes blinded to treatment allocation. Masking procedures are described in SOPs for randomization and vaccine preparation and administration. The FMP2.1/AS02A vaccine will have an opaque milky white appearance. The comparator rabies vaccine will appear as a clear to slightly opaque, colorless suspension after reconstitution. Therefore, blinding of the individuals preparing the study vaccine ("study pharmacists") will not be possible. Since the test article and comparison vaccines can be distinguished by appearance, the vaccine preparation area and the immunizing area will be physically separated. The study pharmacist and his assistant are both experienced pharmacists, and they will be exclusively dedicated to vaccine preparation.

Immunizations will be carried out simultaneously in dedicated vaccination rooms adjacent to the vaccine preparation room and connected by sliding doors. Despite the fact that the volumes of the study vaccine preparations are different, every attempt will be made to maintain blinding. The syringe barrels will be covered with opaque tape. Vaccinators will be physicians who are not involved in any way with surveillance activities, so that even if they realize which vaccine they are injecting, they will not be involved in the assessment of adverse events following vaccination. Each participant will be vaccinated in a closed room out of view of anyone other than the vaccinators, so that each parent sees only the syringe her child is injected with and never sees other participants being injected. The parents will not be told that the vaccines vary with respect to volume.

The Statistician at the EMMES Corporation in the US will also have the randomization list. The Local Medical Monitor will be provided sealed code-break envelopes and may unblind herself to the vaccine allocation of individual study participants if deemed urgently necessary for medical and/or ethical reasons (for example, in the case of a participant in urgent need of rabies immunization). The Local Medical Monitor (LMM) will also keep one set of the randomization code in a sealed envelope, in the event that emergency unblinding is required. USAMMDA will also be provided a sealed copy which will be held by the Division of Medical Affairs. Access to unsealed copies of the randomization list will be exclusively limited to the study pharmacists and the EMMES Corporation statistician. These individuals will be unblinded and will not be involved in study participants' further evaluation.

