### **6.2.1 Administration of vaccines**

Vaccines will be administered by physician-investigators not involved with assessing adverse events. Each 0.1, 0.25 or 0.5 mL of FMP2.1/AS02A or 1.0 mL of rabies vaccine will be administered by intramuscular injection in the left deltoid muscle immediately after formulation/reconstitution. Each vial will be used for only one dose for one participant. Alternatively the right deltoid muscle may be used when the preferred site for injection is contraindicated or not advisable such as in the case of a condition involving pain, infection, scarring that will make local reactions difficult to assess, or if the study participant or parent/guardian declares a preference for immunization in the alternative site.

For each cohort, immunizations will begin with children aged 2 years or older. Children aged less than two years will not be immunized until at least a day after the first immunizations are given to older children.

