### **10.2.3 Recording adverse events**

At each visit/assessment, the investigator will evaluate all adverse events observed by the investigators or reported by the participant or their parents/guardians. New adverse events will be recorded in the Adverse Event form within the participant's CRF. Solicited and unsolicited adverse events will be recorded on separate pages of the CRF. The nature of each event, date and time (where appropriate) of onset, outcome, intensity and relationship to vaccination will be established. Any corrective treatment will be recorded in the CRF. As a consistent method of soliciting adverse events, the participant and their parents/guardians will be asked a non-leading question such as: "Have you felt different in any way since receiving the vaccine or since the last visit?" The investigator will record only those adverse events having occurred within the time frames defined above.

Adverse events already documented in the CRF, *i.e.* at a previous assessment and designated as 'ongoing' will be reviewed at subsequent visits, as necessary. If these events have resolved, the documentation in the CRF will be completed, including the date that the adverse event resolved. If an adverse event changes in frequency or intensity during a study period, the record will be updated to reflect the maximum intensity or describe the frequency.

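### Section 5.4.2 leaves a residual route of unblinding: each parent may see her own child's syringe, although injected volumes differ 2- to 10-fold between the arms of a cohort

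*Protocol*

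**What the plan says.** Section 5.4.2 intends parents, clinical investigators and all staff who measure outcomes to be blind. It recognises the problem of unequal volumes: "Despite the fact that the volumes of the study vaccine preparations are different, every attempt will be made to maintain blinding". The safeguards that it lists are:

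- "The syringe barrels will be covered with opaque tape".
- "Each participant will be vaccinated in a closed room out of view of anyone other than the vaccinators", and, in the same sentence, "each parent sees only the syringe her child is injected with and never sees other participants being injected".
- Families are kept unaware that the two products differ in volume.
- Vaccinators take no part in surveillance. The stated reason is that they may work out which product they are giving.

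The section refers to SOPs for further masking detail. Those SOPs are not part of the protocol text.

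Section 6.2.1 gives the volumes: "Each 0.1, 0.25 or 0.5 mL of FMP2.1/AS02A or 1.0 mL of rabies vaccine will be administered by intramuscular injection".

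On the assessment side, section 7.4 has investigators take symptoms from participants and parents during at least an hour of observation after each injection, and visits follow on days 1, 2, 3 and 7. Section 10.2.3 has the investigator evaluate "all adverse events observed by the investigators or reported by the participant or their parents/guardians".

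**The concern.** The children are aged 1 to 6 years, so much of the symptom information reaches the assessor through the parent. She is a main informant for the primary endpoint, and 5.4.2 has her see the one object that carries information about the arm.

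Not telling parents about the volumes, and hiding other injections from them, removes the comparison that a parent would need to guess the product. It does not protect the assessor. A clinician who works from this protocol can know that there are only two volumes in a cohort, and needs no comparison child to interpret a remark that the injection was large or tiny.

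What is at stake is the softer part of the safety comparison. Irritability, drowsiness, loss of appetite and vomiting are graded on behaviour and intake (Table 11). Causality of every event other than a solicited local reaction is a yes/no opinion of the investigator (10.4). Symptom incidence is to be compared between groups by Fisher's exact test (12.5.3), and a vaccine-related SAE within the seven-day window pauses immunization (10.9).

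**Working it through.** The protocol states no figure for the quality of the blind, so there is nothing to reproduce. Three checks apply.

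**1. Volume ratios.** Inputs are from section 6.2.1. Ratio = rabies volume / FMP2.1/AS02A volume.

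| Cohort | FMP2.1/AS02A | Rabies | Ratio |
|---|---|---|---|
| 1 | 0.1 mL | 1.0 mL | 1.0/0.1 = 10 |
| 2 | 0.25 mL | 1.0 mL | 1.0/0.25 = 4 |
| 3 | 0.5 mL | 1.0 mL | 1.0/0.5 = 2 |

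**2. What one remark could tell an assessor.** Allocation is 3:1 in every cohort (5.4.1; for example, "Cohort 1 will be randomized in a 3:1 ratio"), so the prior probability of rabies vaccine is 0.25. Assume that a remark of large or small is right with probability a in both arms. The protocol gives no value for a, so a range is shown.

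- P(rabies | large) = 0.25a / [0.25a + 0.75(1 − a)]
- P(FMP2.1 | small) = 0.75a / [0.75a + 0.25(1 − a)]

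| a | P(rabies given large) | P(FMP2.1 given small) |
|---|---|---|
| 0.50 (no information) | 0.25 | 0.75 |
| 0.60 | 0.33 | 0.82 |
| 0.75 | 0.50 | 0.90 |
| 0.90 | 0.75 | 0.96 |
| 1.00 | 1.00 | 1.00 |

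For a = 0.75: 0.1875 / (0.1875 + 0.1875) = 0.50. For a = 0.90: 0.225 / (0.225 + 0.075) = 0.75.

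A fairly accurate remark moves the assessor's belief a good deal. It settles the matter only when a = 1. It is reasonable to expect a to be highest at 10:1 and lowest at 2:1. The table is conditional on a remark being made, and the protocol offers nothing from which to estimate how often that would be.

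**3. The wording of 5.4.2 set side by side.** The first half of the sentence puts the vaccination "Each participant will be vaccinated in a closed room out of view of anyone other than the vaccinators". The second half says "each parent sees only the syringe her child is injected with and never sees other participants being injected". Taken literally, both cannot be true of a parent. The first half may be meant to exclude other families only, but it does not say so.

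The section also treats two people differently. The vaccinator may recognise the product from the taped syringe, and is therefore kept away from outcome assessment. The parent sees the same syringe, with less to go on, and then takes part in outcome reporting. No corresponding barrier is stated for her.

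**The case against.** The other side has a good case, and much of it stands.

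- **The risk is recognised and mitigated.** Section 5.4.2 names the volume difference and lists several safeguards. The clause about the parent's view is itself meant as one, because it denies her a comparison. This stands: the plan does not neglect the issue.
- **The physical detail is unknown.** Syringe size and the extent of the tape are not given, and the SOPs may cover positioning and staff conduct. Whether plunger position or injection time betrays the volume is therefore inference. This stands, and it limits the point to a residual risk.
- **One remark need not unblind.** A reader might infer that a single comment from a parent reveals the allocation. The documents do not support that. The parent has no reference, must judge volume without error, and must mention it.
- **Part of the endpoint is less exposed.** Swelling and erythema are graded in millimetres and fever in degrees. Pain is graded by reaction to touch or movement, with the site examined at the visits. Solicited local reactions count as related by rule. The trial is not powered for group differences, and the 10 µg level, where the ratio is largest, is not a candidate for further development (12.4). All of this narrows the consequence but leaves behavioural symptoms and causality judgements exposed.
- **Reactogenicity may hint at the arm anyway.** In the Malian adult trial (Table 7), swelling reports totalled 7 + 24 + 6 = 37 and 3 + 12 + 21 = 36 in the two FMP2.1 groups, against 3 + 3 + 5 = 11 with rabies vaccine. That is true, but it is no reason to leave open a second route that is easily closed.
- **Warning parents could backfire.** Asking parents not to describe the injection would signal that its appearance matters. This stands, and the fix avoids it.

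**Conclusion.** The point holds as a cheap improvement to a stated procedure, not as a demonstrated failure of the blind. Section 5.4.2 lets an informant for the primary endpoint see a syringe whose content differs in volume by 10:1, 4:1 or 2:1 between the arms of her child's cohort. The stated safeguards protect her blind better than they protect the assessor's. The sentence that describes who can see the injection contradicts itself and needs rewording in any case.

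The conclusion rests on two assumptions: that some visible cue to volume survives the tape, and that assessors know the volumes in the protocol. Neither the frequency of such remarks nor the resulting bias in symptom rates can be derived from the document. A reader might go further and conclude that the reactogenicity comparison is biased by some stated amount, or that the plan overlooked the volume difference. The text supports neither conclusion.

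**What to change.** Reword 5.4.2 and the vaccine administration SOP as follows:

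- Keep the syringe out of the parent's and child's line of sight before, during and after the injection. They can face away, or a simple screen can be used, with the syringe discarded before they turn.
- Delete the clause saying that the parent sees her child's syringe. This also removes the internal conflict.
- Instruct assessors not to ask about or discuss the injection itself.
- Give parents no instruction that would suggest that volume matters.

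Matched syringe sizes or plunger covers should not be required on this evidence, because their value depends on equipment details that the protocol does not give.

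The cost is a short text change and slightly longer handling per injection. Dose, volume, staff and sample size do not change. The change has to be made before vaccination starts, since a blind lost at injection cannot be restored in the analysis.
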